# Caudal epidural steroid injections versus selective nerve root blocks for single-level lumbar spinal stenosis: a study protocol for a randomized controlled trial

**DOI:** 10.1186/s13063-021-05485-1

**Published:** 2021-08-09

**Keywords:** Caudal epidural steroid injections, Selective nerve root blocks, Lumbar spinal stenosis, Randomized controlled trial

## Abstract

**Background:**

Lumbar spinal stenosis (LSS) is a common degenerative condition associated with old age. Its incidence continues to increase with the rapidly aging population in China. Treatment for LSS usually begins with conservative treatments, as some patients refuse surgical procedures or have surgery contraindications. Caudal epidural steroid injections (CESIs) and selective nerve root blocks (SNRBs) are two commonly used conservative treatments for LSS, which have proven to be effective at relieving LSS symptoms in many studies. However, there are no randomized controlled trials comparing these two procedures. We planned the first study to assess which one of these two procedures is more effective in treating LSS. We will compare the efficacy of these two treatment methods in terms of duration of symptom relief and recurrence rate. We hope our findings will help clinicians choose an optimal treatment for LSS patients.

**Methods/design:**

We plan to conduct a 1-year randomized controlled trial that will include a total of 76 subjects. They will be randomly divided into two groups: group A (patients will receive CESIs) and group B (patients will receive SNRBs). Two days before the procedure, we will assess these patients using the Leeds Assessment of Neuropathic Symptoms and Signs (LANSS) pain scale, Oswestry Disability Index (ODI), and numeric rating scale (NRS) for pain. One day, 2 weeks, 3 months, 6 months, and 1 year after the procedure, we will assess the condition of these patients again with the NRS and ODI.

**Discussion:**

We hope our findings will lay the foundation for the design of further comprehensive studies and help clinicians make a choice between CESIs and SNRBs for LSS patients.

**Trial registration:**

Chinese Clinical Trial Registry ChiCTR1900028038. Registered on 8 December 2019

## Background

Lumbar spinal stenosis (LSS) is a lower back condition where the central canal, lateral recess, or neural foramina becomes narrowed. Common LSS symptoms are lower back pain, burning pain in the buttocks or legs, weakness, numbness or tingling, and loss of sensation [1]. However, some people with LSS may be asymptomatic. Other patients may have to lean forward to relieve pain while walking, but physical examination often fails to find positive signs [2]. LSS is typically caused by degenerative arthritis, and less common causes include space-occupying lesions and fibrosis. The prevalence of LSS is estimated to be 47.2%, and its classical symptoms are neurogenic claudication and lower back pain [3].

Given that the causes of LSS tend to differ among different patients, doctors need to determine how and why a patient develops LSS in order to formulate a treatment plan that works best for him/her. The main pathogenesis of LSS is inflammatory changes around the nerve roots, congestion, and edema, which is also an important cause of root pain and the theoretical basis for corticosteroid injection to improve clinical symptoms [4–6]. Ma et al. believed that long-term inflammation, chronic strain, ligamentum flavum, and facet hypertrophy reduce the normal space available for nerves in the spinal canal and result in direct pressure on nerve roots causing lower back pain [7]. Chagnas et al. pointed out that LSS is secondary to facet joint osteoarthritis, ligamentum flavum hypertrophy, and/or bulging of the intervertebral disc that leads to narrowing of the spaces around neurovascular structures of the spine [8].

To provide a scoring system that can guide LSS treatment and based on the pathogenesis and imaging characteristics of LSS, researchers have proposed the following grading system: grade 0—a normal intervertebral foramen; grade 1—mild foraminal stenosis with perineural fat obliteration in either the transverse or vertical direction; grade 2—moderate foraminal stenosis with perineural fat obliteration in both the transverse and vertical directions; and grade 3—severe foraminal stenosis with nerve root collapse or morphologic change [9, 10].

Most patients seeking treatment for lower back pain have LSS. Treatments for LSS can be conservative and surgical. Conservative management is successful in most patients and is recommended as first-line treatment. Common conservative treatments for LSS include caudal epidural steroid injections (CESIs) and selective nerve root blocks (SNRBs). The reasons for their popularity among primary care physicians are as follows: First, compared with conventional surgical interventions, SNRBs and CESIs greatly reduce the time that physicians are exposed to X-rays, thus protecting their health. Second, SNRBs and CESIs are easy to perform and have a short learning curve.

The efficacy of CESIs has been demonstrated in many studies. Delport et al. analyzed 140 patients treated with epidural steroid injection (ESI) [11]. Fifty-three percent reported improvement in their functional abilities and 74% were at least somewhat satisfied with ESI as a form of treatment. Fukusaki et al. conducted a prospective, randomized, double-masked trial evaluating the efficacy of ESI in 53 patients with LSS [12]. The patients were randomized into three groups: epidural saline injection, epidural local anesthetic, and epidural anesthetic plus steroid. They found that there was a significant difference in the efficacy of the different treatments at 1 month. However, after 3 months, there was no significant difference between the three groups, proving the short-term effect of ESI. Koc et al. reported findings from a prospective, randomized controlled trial of 33 patients comparing the effects of ESI and a conservative inpatient physical therapy program on pain and function for patients with LSS [13]. They found that the ESI group had significant improvement in visual analog scale (VAS) scores at the 2-week follow-up. They concluded that ESI and physical therapy are equally effective in treating LSS up to 6 months of follow-up, while ESI has better short-term efficacy.

A selective nerve root block (SNRB) is a minimally invasive procedure; a needle is inserted into the epidural space in the foramen at the suspected spinal level, and medications such as steroids and local anesthetics are then injected into the area of a specific nerve root [14]. This procedure is considered a very safe and effective treatment option for spinal neuropathy and chronic back pain [15, 16]. Zhang et al. performed SNRBs in 56 LSS patients and found that 80% of them achieved excellent short-term surgery outcomes [17]. Weiner et al. analyzed 30 patients with herniated discs who underwent nerve root blocks and noted immediate relief in 27 patients. During 1–10 years of follow-up, 22 patients (79%) experienced substantial and permanent pain relief [18]. Martin et al. retrospectively analyzed 30 (20 disc herniations, 10 foraminal stenoses) patients with minor sensory/motor deficits who were treated with a SNRB [19]. They found that 87% of patients had rapid and significant regression of pain in 1–4 days, and 60% had permanent resolution of pain. Therefore, they believe that SNRBs are very effective in treating lumbar neuropathy and recommend them as the treatment of choice for this condition.

Narrowing of the spinal canal caused by lumbar spine degeneration usually occurs slowly, over many years or decades. Substantial narrowing compresses the spinal nerves, which causes symptoms including pain at the early stage, and numbness and weakness of the extremities at the middle and late stages, severely affecting patients’ quality of life. Therefore, doctors should aim for early-stage interventions, offer effective treatments in the middle stage, and absolutely avoid late-stage surgery. In addition, it is recommended that patients in need of conservative treatments receive interventions as early as possible to prevent exacerbation of lumbar neuropathy.

It follows from the above that both CESIs and SNRBs can effectively relieve clinical symptoms and improve neurologic function in patients with LSS. SNRBs are different from epidurals. Instead of administering medication to cover all the nerve roots, selective blocks are performed to target a particular pinched nerve root. SNRB injections can therefore be performed to manage a specific area of pathology without causing damage to nearby normal nerve tissues.

To our knowledge, however, there have been no randomized controlled trials comparing the efficacy of SNRBs and CESIs. In clinical practice, primary care physicians often have to choose between a selective nerve block and a caudal epidural injection based on their own experience, as there is no guideline for them to refer to. To fill this gap, we plan to conduct the first study to compare the effects of SNRBs and CESIs on LSS. We will use outcome measures such as duration of symptom relief and recurrence rate to determine whether SNRBs or CESIs are more effective. We hope our findings will help physicians make a choice between SNRBs and CESIs for LSS patients.

### Hypothesis

Our hypothesis is that SNRBs have a lower recurrence rate than CESIs in treating patients with single-level LSS.

## Methods/design

This is a randomized controlled trial, aimed at comparing the recurrence rate of LSS following treatment with SNRBs and CESIs in patients with one-level LSS. This study was approved by the Ethics Committee of the Fourth School of Clinical Medicine of Xinjiang Medical University and will be conducted in accordance with the World Medical Association Declaration of Helsinki. This study is registered in the Chinese Clinical Trial Registry (Registration No. ChiCTR1900028038). Written informed consent will be obtained from all patients before initiating treatment.

Evaluation of the results and statistical analysis will be performed by professionals who are blinded to the group assignment. Participant flow is shown in Fig. 1. The study will last for 1 year. Patients will be randomly divided into two groups with patients in group A receiving a CESI and patients in group B receiving an SNRB.

**Fig. 1 Fig1:**
[figure not shown]
Schematic presentation of patient flow. LSS, lumbar spinal stenosis; CESI, caudal epidural steroid injection; SNRB, selective nerve root block; NRS, numeric rating scale; ODI, Oswestry Disability Index; LANSS, Leeds assessment of neuropathic symptoms and signs

The main outcome measures include the Leeds Assessment of Neuropathic Symptoms and Signs (LANSS) pain scale to determine whether the pain experienced is due to nerve damage, the Oswestry Disability Index (ODI) to assess functional status, and a numeric rating scale (NRS) for pain to evaluate pain intensity [20]. Two days before the procedure, we will assess the condition of patients using the LANSS pain scale, ODI, and NRS for pain. One day, 2 weeks, 3 months, 6 months, and 1 year after the procedure, we will evaluate these patients again using the NRS for pain and the ODI.

### Recruitment

First, we will assess the potential candidates and inform them of our study procedure. We will randomly divide the eligible patients into two groups after obtaining written informed consent from each patient. Treatment will be given to each patient based on the group he/she is in.

### Sample size

Because the present study is a clinical application, according to the actual situation, it is difficult to calculate the sample size by pre-experiment, so we finally decided that the sample size of this study was obtained from the previous relevant literature data. The sample size outcome effect size is based on studies found in the literature using the ODI and NRS scores [21]. The mean change of ODI and NRS in group B is expected to be 93% and 0–1 scores, while in group A it is expected to be 80% and 3–4 scores. The sample size was calculated using the sample size formula for a quantitative equivalence trial: *n* = 2(*Z*_*α*_ + *Z*_*β*_)^2^*δ*^2^/(*D* − Δ)^2^ (*α* = 0.05, *β* = 0.2). After we entered *δ* of 2.17, *D* of 0.1, and *Δ* of 1.2 into the formula, we found that it required 31 patients in each group. Given a loss to follow-up rate of 20%, approximately 76 subjects are required.

This experiment was conducted simultaneously in the Second Spine Department of the Fourth School of Clinical Medicine of Xinjiang Medical University and Spine Department of the First Affiliated Hospital of Shihezi University, and inpatients meeting the inclusion criteria were included in the study.

Since the LSS patient base of the above two departments is large enough to recruit subjects at the same time, there is no need to worry about the sample size. Some benefits can also be provided to patients participating in the study to supplement the sample size (such as free professional counseling, functional exercise instruction)

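### The sample size formula is labelled for equivalence but guards one margin only, so β = 0.2 does not describe the power to conclude equivalence: about 40% or 17% at the planned 31 per group

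*Protocol article*

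**What the plan says.** The Sample size section names the method: "The sample size was calculated using the sample size formula for a quantitative equivalence trial". The formula, in plain notation, is n = 2(Zα + Zβ)²δ²/(D − Δ)², with α = 0.05 and β = 0.2. The result, a number per group, follows: "After we entered *δ* of 2.17, *D* of 0.1, and *Δ* of 1.2 into the formula, we found that it required 31 patients". From this the section derives the total: "Given a loss to follow-up rate of 20%, approximately 76 subjects are required".

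The section does not define δ, D or Δ, does not say whether α is one- or two-sided, and gives no second margin. It also lists expected NRS values of 0–1 in the nerve root block group and 3–4 in the caudal injection group.

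The Hypothesis section is directional: "Our hypothesis is that SNRBs have a lower recurrence rate than CESIs".

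**The concern.** A conclusion of equivalence requires the data to exclude a difference beyond the margin in each direction. The printed formula has one distance in the denominator and Zβ, not Zβ/2, in the numerator. That is the formula for a one-sided, one-margin comparison (non-inferiority). It approximates equivalence power well only when the other margin is so far away that it is almost never missed. Here the assumed difference is 0.1 and the margin 1.2, so the two margins lie 1.1 and 1.3 from the assumed truth, and the farther one matters nearly as much as the nearer.

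The β in the paragraph therefore does not belong to the design the paragraph names. A reader would take an inconclusive equivalence result as coming from a trial with 80% power, when on the protocol's own inputs it had much less. This is distinct from the question whether 31 follows from the formula: correcting that alone would leave the wrong power attached to the label.

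**Working it through.** **Inputs (Sample size section).** δ = 2.17, D = 0.1, Δ = 1.2, α = 0.05, β = 0.2, 31 per group. Assumed here because the text does not say: δ is the common SD, D the true difference, and Δ a symmetric margin of ±1.2. The reverse reading (margin 0.1, true difference 1.2) makes no sense for equivalence. As sidedness is not stated, both Zα = 1.645 and Zα = 1.96 are shown; Zβ = 0.842.

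**1. The plan's own figure.**
- Zα = 1.645: 2 × (1.645 + 0.842)² × 2.17² / 1.1² = 48.12, so 49 per group.
- Zα = 1.96: 2 × (1.96 + 0.842)² × 2.17² / 1.1² = 61.09, so 62 per group.
- The stated 31 is not reproduced. It appears if the leading 2 is dropped in the second line (61.09 / 2 = 30.55, so 31), or equivalently if 62 is read as the total.
- Loss to follow-up: 31 × 1.2 = 37.2, so 38 per group and 76 in total, as stated.

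**2. Power formulas (normal approximation).** SE = 2.17 × √(2/n).
- One margin: Φ(1.1/SE − z).
- Both margins: Φ(1.1/SE − z) + Φ(1.3/SE − z) − 1.

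**3. At the planned 31 per group.** SE = 2.17 × √(2/31) = 0.551.
- One-sided 0.05 per margin: near margin 63.7%, far margin 76.2%, both 39.9%.
- One-sided 0.025 per margin: near margin 51.4%, far margin 65.5%, both 16.9%.

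**4. At the size the printed formula yields.**

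| n per group | z used in sizing | z used per margin | Near margin | Far margin | Both |
|---|---|---|---|---|---|
| 49 | 1.645 | 1.645 | 80.6% | 90.7% | 71.3% |
| 62 | 1.96 | 1.96 | 80.6% | 91.6% | 72.1% |
| 62 | 1.96 | 1.645 | 88.1% | 95.5% | 83.5% |

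The first two rows use one α throughout. The near-margin column shows that the formula does deliver about 80%, but for one margin. The far margin is missed 8–9% of the time, and that is the shortfall. The third row sizes at one α and tests at another, which lifts the joint power above 80%.

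**5. Checks.** With the t distribution, the two-margin powers are 70.5% (n = 49) and 71.1% (n = 62) in the first two rows, and 38.3% and 15.4% at n = 31. Simulation of 100,000 trials with t-tests gives 70.6% and 71.4% for the first two rows.

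**6. The section's expected NRS values.** The closest they come is 3 − 1 = 2 points apart, outside ±1.2. If the formula is on the NRS scale, which is not stated, power to show equivalence under a 2-point difference at 31 per group is Φ((1.2 − 2)/0.551 − 1.645) = Φ(−3.10), about 0.1%.

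**The case against.** **The trial does not seek equivalence.** The word occurs once, as the name of a formula. No equivalence conclusion or confidence interval rule is planned, the hypothesis is directional, and the Background and Discussion ask which procedure is more effective. This stands, and it shapes the fix: refining equivalence power alone would polish the power of the wrong test. It does not make the paragraph correct, because equivalence is the only design to which the protocol attaches its β.

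**The larger loss comes from the arithmetic.** At 31 per group, one-margin power is already 64% or 51%, so the 80% is gone before the second margin is considered. This also stands. The second margin then takes the figure down to 40% or 17%.

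**The shortfall at the formula's own size depends on an unstated testing rule.** With 62 per group and one-sided 0.05 per margin, joint power is 83.5%. The protocol states neither that rule nor any other, so the 71–72% must carry its condition.

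**The margin is an inference.** The section never uses the word and defines no symbol. The reading adopted here is the sensible one, but it is an assumption.

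**Relabelling as non-inferiority would not be enough.** It would still not support a hypothesis of lower recurrence. This is accepted.

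**Conclusion.** The point holds in a limited form. The Sample size section attaches β = 0.2 to an equivalence label, while its formula protects one margin. At the planned 31 evaluable per group, power to exclude both ±1.2 is about 40% (one-sided 0.05 per margin) or 17% (one-sided 0.025). These figures rest on δ as SD, D as true difference, Δ as a symmetric margin, and the normal approximation.

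Three stronger readings are not supported:
- A reader might infer that this trial has 71–72% equivalence power. Those figures belong to 49 or 62 per group, sizes the protocol never plans, and they require the same α for sizing and testing.
- A reader might infer that every corrected version of the formula falls short of 80%. It does not: 62 per group tested at one-sided 0.05 per margin gives 83.5%.
- A reader might infer that the trial is set to draw an equivalence conclusion at low power. The protocol plans no such conclusion; its hypothesis is lower recurrence with nerve root blocks.

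The correction is worth making because the stated error rate is wrong for the claim it accompanies, and because the label, the hypothesis and the expected values in the protocol point in different directions.

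**What to change.** In the Sample size section:

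1. Withdraw the implied 80% power for equivalence.
2. Define δ, D and Δ, name the outcome and scale they refer to, and state the sidedness of α.
3. Remove the equivalence label, since the hypothesis is directional and the expected NRS values differ by at least 2 points. Restate the power that the planned 31 evaluable per group (76 in total) gives for the directional comparison. The protocol gives no expected recurrence rates, so the rates used must be stated as assumptions, with power shown over a range.
4. If equivalence is really intended, report the two-margin power (about 40% or 17% at 31 per group, according to α) and reconcile it with the hypothesis and the expected values.
5. In either case, make no equivalence claim unless the whole confidence interval, at a level matching the chosen α, lies within ±1.2.

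The cost is a rewritten paragraph and a less favourable stated power. The planned number of patients does not change.

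### The sample size rests on an equivalence formula for a score, while the hypothesis is superiority on recurrence; the stated 80% power does not apply to that hypothesis, and 31 per group does not follow from the printed formula

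*Protocol article*

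**What the plan says.** **Question.** The Hypothesis section reads "Our hypothesis is that SNRBs have a lower recurrence rate than CESIs in treating patients with single-level LSS". The opening of Methods/design describes a trial "aimed at comparing the recurrence rate of LSS following treatment with SNRBs and CESIs". The Discussion says the recurrence rate will be used to decide which procedure relieves symptoms better in the long term. Outcome measures lists ODI, NRS and recurrence together as main outcomes, derives recurrence from the two scores through Table 4, and gives recurrence particular weight.

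**Sizing.** Under Sample size, "The sample size was calculated using the sample size formula for a quantitative equivalence trial". In plain notation the formula printed there is n = 2(Zα + Zβ)²δ²/(D − Δ)², used with α = 0.05 and β = 0.2. The inputs are reported as "After we entered *δ* of 2.17, *D* of 0.1, and *Δ* of 1.2 into the formula". The result is given as 31 per group, which is then raised for dropout: "Given a loss to follow-up rate of 20%, approximately 76 subjects are required". The three symbols are not defined, the score they belong to is not named, and the sidedness of α is not given.

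**Expected results.** The same paragraph says "The mean change of ODI and NRS in group B is expected to be 93% and 0–1 scores", and for group A it gives 80% and 3–4. Group B is SNRB and group A is CESI.

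The article gives no expected recurrence rate and no power for recurrence.

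**The concern.** There are three separate problems.

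1. **Design and endpoint.** An equivalence calculation on a continuous score asks how many patients are needed to show that two means are close. The hypothesis asks whether one proportion is lower than another. Power for the first says nothing about the second.
2. **Inputs.** The calculation appears to assume almost no difference between arms, while the paragraph around it expects a clear one.
3. **Arithmetic.** The stated n should follow from the stated formula, and it does not.

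A reader of the eventual report would take 80% as the chance of detecting a worthwhile difference in recurrence. If that chance is much lower, a null result on recurrence says little, and the equivalence label in the sample size section would make it easier to over-read.

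**Working it through.** **Step 1: the plan's own figure.** Inputs from Sample size: δ = 2.17 (in the position of the standard deviation), D = 0.1, Δ = 1.2, α = 0.05, β = 0.2. Then δ² = 4.7089 and (D − Δ)² = 1.21.

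- One-sided α: 2 × (1.645 + 0.842)² × 4.7089 / 1.21 = 48.1, so 49 per group.
- Two-sided α: 2 × (1.960 + 0.842)² × 4.7089 / 1.21 = 61.1, so 62 per group.
- One-sided α with β/2, as is common for two one-sided tests: 66.7, so 67 per group.

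None gives 31. Dropping the leading 2 at two-sided α gives 61.09 / 2 = 30.55, which rounds to 31. This may be how 31 arose, for example by taking the per-group result as a total, but the article does not say.

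The total of 76 is 2 × 38, from 31 × 1.2 = 37.2. Dividing by 0.8 instead gives 39 per group, or 78. That difference is minor.

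**Step 2: power for equivalence with 31 per group** (normal approximation, true difference 0.1, margin ±1.2, SD 2.17).

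- Standard error = 2.17 × √(2/31) = 0.551.
- Single bound, one-sided 0.05: Φ(1.1/0.551 − 1.645) = Φ(0.35) = 64%.
- Both bounds: 0.637 − Φ(−1.3/0.551 + 1.645) = 0.637 − 0.238 = 40%.

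**Step 3: inputs against the expected results.** NRS 0–1 against 3–4 is a gap of 3 points between midpoints, with a range of 2 to 4. Because (D − Δ)² is symmetric, exchanging D and Δ leaves n unchanged, and neither 0.1 nor 1.2 matches 2 to 4 points. If D and Δ are NRS points, a true gap of 2 to 4 gives at most a 0.1% chance of concluding equivalence within ±1.2 at 31 per group.

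**Step 4: power for the stated hypothesis.** Pooled two-proportion test, two-sided 0.05. The recurrence rates are assumptions, because the article gives none.

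| CESI vs SNRB recurrence | Power, 31 per arm | Power, 38 per arm | n per arm for 80% |
|---|---|---|---|
| 50% vs 30% | 36% | 43% | 93 |
| 50% vs 25% | 53% | 62% | 58 |
| 40% vs 20% | 40% | 48% | 82 |
| 30% vs 15% | 29% | 34% | 121 |
| 40% vs 10% | 79% | 87% | 32 |

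With 31 per arm, 80% power is reached at 50% vs 17%, 40% vs 9.8% and 30% vs 3.8%. These are differences of about 33, 30 and 26 points. At 50% vs 30%, the 95% confidence interval half-width is 1.96 × √((0.25 + 0.21)/31) = 0.24, or 24 points.

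**Step 5: power for superiority on NRS, if 2.17 is its SD.** The difference detectable at 80% power with 31 per arm is 2.802 × 0.551 = 1.5 points. Power for a 2-point difference is 95%.

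**The case against.** **The meaning of D and Δ is inferred.** An expected difference of 0.1 and a margin of 1.2, in NRS points, is the usual reading of such a formula, but the article does not state it. A reader might infer that equivalence is false by the plan's own assumptions. That goes too far, because it depends on both the meaning and the scale. What stands is that the inputs are undefined and that neither value matches the stated NRS gap.

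**The expected values are labelled as mean changes.** Taken literally, an NRS change of 0–1 after SNRB against 3–4 after CESI would favour CESI, against the hypothesis. They read more naturally as end scores. The gap is about 3 points either way, but the label is part of what needs clearing up.

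**The size is not useless.** A reader might infer that 31 per arm bears no relation to anything the trial wants to conclude. The document does not support that: NRS is a named main outcome and feeds the recurrence definition. If 2.17 is its SD, 31 per arm is ample for the gap expected (Step 5). The defect lies in the justification and in the absence of planning for recurrence.

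**No equivalence claim is planned.** A reader might also infer that the sponsor intends to report a null result as equivalence. The article uses equivalence only to label the formula, and elsewhere asks which treatment is better. The risk is one of later misreading.

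**Recurrence could be analysed as time to relapse,** since Table 4's note and the Discussion say the time is recorded. This changes little. At 50% vs 30%, a rough log-rank approximation has hazard ratio ln 0.7 / ln 0.5 = 0.515 and 31 × 0.8 = 24.8 events, giving 38% power instead of 36%.

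**Conclusion.** The point holds and should be corrected in the text. The stated 80% power does not apply to the hypothesis on recurrence, and it does not hold for the equivalence calculation either: 49 or 62 per group would be needed by the printed formula, and 31 gives about 40% by two one-sided tests or 64% against a single bound.

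Confidence differs by part. The mismatch between equivalence on a score and superiority on recurrence is explicit in the document. The arithmetic error follows from the printed formula and inputs. The conflict between D or Δ and the 3-point NRS gap rests on reading them as NRS points, which is an inference. The recurrence figures (26 to 33 points detectable; 36% power at 50% vs 30%) rest on an assumed CESI recurrence of 30–50% and about 31 evaluable patients per arm.

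**What to change.** Rewrite the Sample size section as follows.

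1. Remove the equivalence formula and the 80% power claim as the justification for 31 per group.
2. State the design as two-sided superiority, with recurrence by 1 year as the endpoint of the hypothesis.
3. State what the planned size can show. Randomising 76, with 20% loss, leaves about 31 evaluable per arm (38 × 0.8 = 30.4). This detects a recurrence difference of about 26 to 33 points at 80% power if CESI recurrence is 30–50%, and has 36% power at 50% vs 30%. Label the CESI range as an assumption, or replace it with a sourced rate.
4. If NRS is kept as a basis for sizing, define D, Δ, the SD and the score, say whether the expected values are changes or end scores, and reconcile them with the 3-point gap. Give the superiority difference detectable: about 1.5 points at 80% power if 2.17 is the NRS SD.
5. Commit to reporting the confidence interval for the recurrence difference, and state that a non-significant result will not be read as equivalence.

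The cost is the rewriting of one section and a less favourable power statement for the hypothesis. No patients are added. The rewrite discloses the limited power for recurrence but does not cure it.
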